## 3. Discussion

Interest in using probiotics as a constipation-relieving agent is increasing, as approximately half of patients have been disappointed with their current treatments. Probiotics hold great promise as a complementary treatment. However, a clear consensus on its recommendation for a patient with constipation is still unavailable because the existing evidence is limited and the methodology used by the existing studies lacks consistency, precluding a comparison of the results. In this context, we developed the protocol for this study.

The key parameters of the methodology used in the previous RCTs and the present RCT are shown and compared in Table 2. The RCTs cited in Table 2 were obtained from recently published systematic reviews or meta-analyses [39–42, 62, 63] that aim to study the effect of probiotics on constipation. Seventy-six RCTs were initially obtained from these systematic reviews or meta-analyses, while 34 RCTs remained after removing 35 duplicate papers and 7 papers that only focused on the effects of probiotics on intestinal flora in healthy adults for the extraction and comparison of key parameters of the methodology (Table 2). As shown in Table 2, the parameters of the methodology are quite inconsistent. For example, the sample size varies substantially from 8 [64] to 453 [65], and the daily dosage ranges from 10^8^ [66] to 10^10^ [67] CFUs; importantly, the diagnostic criteria for constipation, study stage and duration, and outcomes are also obviously different. Under these circumstances, a high-quality RCT protocol is needed to promote the consistency of methodology in future research. Based on the optimized parameters used by the 34 RCTs (Table 2) and our understanding of methodology, we designed the present protocol, of which the parameters are listed in the last row in Table 2.

We optimize the methodology from the following aspects: ① The general principle for a high-quality RCT is strictly obeyed through the participation of third-party independent companies or the DMT, including randomization, parallel control, blinding, allocation concealment, combination of ITT and PP analyses, consideration of withdrawals or dropouts, replication (enough observed study subjects), and other factors. ② The sample size (100 for each group) is obtained based on the expected difference in weekly frequency of CSBMs between the treatment group and control group, which is sufficient to ensure the reliability and accuracy of the results. The sample sizes in 33 of the 35 previous RCTs are dozens or even several participants, which is probably not sufficient to obtain an accurate result. ③ The latest Rome criteria (Rome IV for the present RCT) are suggested for the diagnosis of chronic constipation to avoid any other self-definition by researchers. ④ Multidimensional outcomes have been observed in the present RCT, including improvements in clinical symptoms, QOL score, emotional status score, and modifications in the gut microbiome and faecal metabolome, to produce a chain of evidence from causal improvements in metagenomic and metabolomic data to clinical symptoms and then to the emotional state and QOL. The outcomes are measured using accepted methods, e.g., BSFS [53], PAC-QOL [57], DASS-21 [58], next-generation sequencing, and LC–MS/MS analysis. Thus, the effects of probiotics on chronic constipation in the present study are more reliable and explainable. ⑤ Other key parameters, such as the study stage and duration, are also suggested.

In addition, the protocol is conducted to prove its feasibility and scientificity by studying the effects of *L. plantarum* P9 on chronic constipation. The study is articulated with a clear testable hypothesis stating that *L. plantarum* P9 improves the clinical symptoms and patient QOL by modifying the intestinal flora. Additionally, the safety of *L. plantarum* P9 will be assessed.

Thus, we believe the study will be a high-quality RCT. The results will be more comprehensive than those of existing studies and will objectively and scientifically reflect the effectiveness of *L. plantarum* P9 on constipation. In addition, the protocol will provide methodological guidance for similar studies, avoiding methodological bias and ultimately facilitating the formulation of a consensus on the use of probiotics as a constipation-relieving agent.

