Only one-fifth of patients with constipation seek medical advice [19], and laxatives are the most frequently prescribed agents [29, 30]. Laxatives, physical exercise, fibre intake, and dietary management are the traditional treatments. However, approximately 50% of constipated individuals are dissatisfied with their current treatments [31, 32]. As many as 74% of nursing home residents have been reported to use laxatives daily [33–35], of which only 28%–57% are estimated to be satisfied with the treatment according to the results of two Internet-based surveys [36, 37]. Undesirable side effects are a main reason for suboptimal satisfaction. New treatments must be developed for unsatisfied patients, and daily intake of probiotics holds great promise since various probiotics have shown benefits for constipation treatment [38–43].

However, although many studies have reported that probiotics are potentially beneficial for constipated individuals [39–43], a clear consensus on the use of probiotics as a constipation-relieving agent has not been reached [44]. This lack of consensus is mainly attributed to the shortage of study methodology in terms of incorrect statistical analysis, inconsistent definitions of constipation and outcomes of the intervention, and an unvalidated assessment technique [44–46]. Therefore, high-quality randomized controlled trials (RCTs) are needed to reach a more confident consensus [47]. Moreover, RCTs examining the effectiveness of probiotics as a constipation-relieving agent may elucidate a clear mechanism of action for a more confident conclusion. Generally, a balanced intestinal flora provides health benefits to human hosts; conversely, an imbalanced flora may promote the development of constipation [48]. Consistently, probiotics may positively modify the intestinal flora [49, 50] and even provide potentially beneficial microorganisms to the host.

Thus, we designed this protocol to study the effectiveness of *L. plantarum* P9 on chronic constipation and to guide other studies assessing the effectiveness of probiotics. The correlation between the clinical improvement of symptoms and changes in intestinal flora was also analysed.

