### 2.9. Secondary Outcomes

Based on the diary (Figure 2), the changes in the percentage of volunteers with a weekly mean frequency of CSBMs ≥3 [32, 54, 55], changes in the weekly mean frequency of spontaneous bowl movements (SBMs) [32, 54–56], weekly mean stool appearance score [53], weekly mean difficulty of passing stool score, and weekly percentage of volunteers who use auxiliary measures to assist with defecation (WPUAMA) will be evaluated each week from day 0 (week 0) to day 14 (week 2), day 28 (week 4), and day 42 (week 6). An SBM is defined as a bowel movement achieved without the use of any drugs or other auxiliary measures during the previous 24 hours [32, 54, 55] (Table 1).The Patient Assessment of Constipation Quality-of-Life (PAC-QOL) questionnaire (Appendix 5 [56, 57]) will be used to evaluate the QOL score on days 0, 14, 28, and 42.The Depression, Anxiety and Stress Questionnaire (DASS-21) [58, 59] (Appendix 6) will be completed online on days 0 (baseline), 14, 28, and 42 and used to assess the participants' emotional status (depression, anxiety, and stress) within the past week (Table 1).For the indicator of the gut microbiome, DNA will be extracted from the stool samples with the QIAamp Fast DNA Stool Mini Kit (Qiagen, Hilden, Germany) according to the manufacturer's instructions, and the quality of DNA will be examined using agarose gel electrophoresis and a NanoDrop spectrophotometer. Shotgun metagenomic sequencing will be performed on all samples using an Illumina HiSeq 2500 instrument. Libraries will be constructed from DNA fragments with a length of ∼300 bp; paired-end reads will be generated by sequencing 150 bp in the forward and reverse directions. Meanwhile, the metagenomic analysis will include several parts: the analysis of alpha diversity and beta diversity in each group to understand whether the differences in the microbiota compositions of groups are significant and a comparison of the taxonomic characteristics of the study group and the control group at the level of phylum, genus, and species to identify specific genes related to the individual differences of constipation. Metagenomic biological pathway analysis will be used to evaluate the effect of probiotics on the function of gut metagenomics in patients with constipation and to explore the metagenomic biological pathways contributing to the mechanism underlying the effect of probiotics on the treatment of constipation.For the indicator of the faecal metabolome, stool samples will be extracted using the protein precipitation method, and the supernatant will be transferred to sample vials for LC-MS/MS analysis. The original data will be subjected to peak alignment, retention time correction, and peak area extraction using the XCMS-Plus program. The structure of metabolites will be identified by accurate mass matching (<5 ppm) and two-level spectrum matching, and the METLIN database will be retrieved. We will then delete data with missing values > 50% in the group, normalize the data, and conduct multidimensional statistical analysis, including unsupervised principal component analysis (PCA), supervised partial least squares discriminant analysis (PLS-DA), and potential differentially abundant metabolite analysis. The metabolomic analysis might further identify the potential differentially abundant metabolites of probiotics in the treatment of constipation, and a correlation analysis between the gut microbiota and metabolites will be performed.

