### 2.14. Data Collection and Collation

The defecation diary (Figure 2) completed by the volunteers will be collected online daily, and the DASS-21 (Appendix 6) will be collected online as scheduled (see Table 1). One stool sample for the gut microbiome analysis and one for the metabolomics test will be collected from each volunteer on days 0 (preadministration period), 28 (administration period), and 42 (postadministration period); these samples will be stored separately and sent for tests at a temperature of −80°C in a special stool storage kit from Guangdong Longsee Company (https://www.longseemed.com).

An independent data management team (DMT) will be established to maintain and monitor study quality and safety. The data of individual characteristics, defecation diary entries (Figure 2), and DASS-21 data (Appendix 6) completed online by volunteers will be downloaded as Excel spreadsheets for further analysis. The gut microbiome and metabolomic data from stool samples will be examined by the Key Laboratory of Dairy Biotechnology and Engineering, Ministry of Education. All data will be submitted to the DMT for management and monitoring. The DMT will promptly analyse the data and contact collectors to resolve any uncertainty that occurs. All records that contain names or other personal information that could identify a participant, such as ID number or consent forms, will be stored separately from the study records. The database will be password protected by the DMT. The team will also have the authority to conduct an interim analysis or terminate the study's next step if the following situations occur: (1) if the probiotic does not affect the gut microbiome, then the study team will not conduct tests on the faecal metabolomes; and (2) if any severe adverse events related to the probiotics occur, the DMT will suggest terminating the study.

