In addition, the statistical analyses of metagenomic and metabolomic data will be performed using *R* software (v.4.0.2) and Adobe Illustrator. PCA and PLS-DA will be performed and visualized using the *R* packages vegan, ggplot, and ggpubr, and the adonis *P* value will be generated based on 999 permutations. The *t*-test, Wilcoxon test, and Kruskal–Wallis test will be used to evaluate differences in variables between and within groups; *P* values will be corrected for multiple testing using the Benjamini–Hochberg procedure. Meanwhile, Pearson's and Spearman's correlation coefficients will be calculated to analyse the correlations between different indicators in clinical, metagenomic, and metabolomic data.

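### The hypothesis that P9 works through the gut flora is paired with plain correlations, which cannot carry the flora-to-symptom link and would mislead if the arms are pooled

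*Protocol article*

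**What the plan says.** - **The claim (protocol article, section 3).** The study is said to rest on a testable hypothesis that P9 "improves the clinical symptoms and patient QOL by modifying the intestinal flora". The range of outcomes is meant "to produce a chain of evidence from causal improvements in metagenomic and metabolomic data to clinical symptoms", and from there to emotional state and quality of life.
- **The linking analyses.** Section 1 describes the work this way: "The correlation between the clinical improvement of symptoms and changes in intestinal flora was also analysed". Section 2.9 adds that "a correlation analysis between the gut microbiota and metabolites will be performed". Section 2.15 says that "Pearson's and Spearman's correlation coefficients will be calculated to analyse the correlations between different indicators in clinical, metagenomic, and metabolomic data". It does not say whether the arms are taken together or separately.
- **The other omics analyses.** Sections 2.9 and 2.15 plan diversity, taxonomic and pathway analyses, PCA, PLS-DA and adonis. The t, Wilcoxon and Kruskal–Wallis tests "will be used to evaluate differences in variables between and within groups", with Benjamini–Hochberg correction. The correlations come in the next sentence, so it is unclear whether the correction extends to them.
- **Timing.** Stool is collected on days 0, 28 and 42 (section 2.14), which are also visit days for the clinical outcomes (Table 1).

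**The concern.** The hypothesis has three links: treatment to flora, treatment to symptoms, and flora to symptoms. Randomisation protects the first two. The third is what makes it a statement about mechanism, and for it the article names only correlation. If P9 changed flora and symptoms by unrelated routes, the trial could still show two significant arm differences and a correlation between them.

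Pooling would make this worse, because arm membership alone then generates a correlation. The design does not guard against it. Day-28 stool is taken at the end of dosing, and taxa are compared down to species level, so the administered species may itself be one of the features. Section 2.14 also makes the metabolome tests conditional on an effect of the probiotic on the microbiome. Flora–metabolite correlations would therefore be computed only where the first condition for the artefact is met.

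At stake is a reported mechanism that the data cannot show, in a protocol that section 3 offers as a methodological guide for similar studies.

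**Working it through.** **1. Plan's own figure.** Section 2.12 gives a difference of 3, SD 6, α 0.05 and β 0.20. With a two-sided α, n per group = 2 × (1.960 + 0.842)² × 6² / 3² = 2 × 7.85 × 4 = 62.8, so 63, as stated. The standardised clinical effect is dY = 3/6 = 0.5.

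**2. Inputs.**
- Participants: 100 per group, or 80 per group after the plan's 20% drop-out (total 200 or 160).
- Feature shift dM, in SD units: not in the document. Assumed, with a range of 0.2 to 2.
- Within-arm correlation: set to zero, so that any correlation found is an artefact.
- Arms pooled: assumed for this calculation only.

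**3. Expected pooled correlation.** With equal arms, the arm indicator has variance 1/4. The pooled covariance is then dM·dY/4 and the pooled variances are 1 + dM²/4 and 1 + dY²/4, giving

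r = (dM·dY/4) / √[(1 + dM²/4)(1 + dY²/4)].

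For dM = 2 and dY = 0.5: r = 0.25 / √(2 × 1.0625) = 0.25/1.458 = 0.171.

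**4. How often it is significant.** Simulation with normal variables, 40,000 trials per setting, Pearson test at 0.05 for one feature, before any multiplicity correction (simulation error at most about 0.5 percentage points):

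| Feature shift (SD) | Expected r | Pooled, n = 160 | Pooled, n = 200 | Adjusted for arm |
|---|---|---|---|---|
| 0.2 | 0.02 | 6.2% | 6.2% | 5% |
| 0.5 | 0.06 | 11.5% | 13.0% | 5% |
| 0.8 | 0.09 | 20.7% | 24.8% | 5% |
| 1.0 | 0.11 | 28.1% | 33.2% | 5% |
| 1.5 | 0.15 | 45.8% | 54.8% | 5% |
| 2.0 | 0.17 | 59.6% | 69.5% | 5% |

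In a smaller run of 2,000 trials per setting, Spearman gave nearly the same rates (58% and 70% at 2 SD). Correlation within the active arm alone stayed at about 4–6%.

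**5. Stricter threshold.** At an illustrative p < 0.001, the pooled rates fall to 13–19% for a 2 SD shift and 3–4% for 1 SD.

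**6. Change scores.** Let M and Y be changes from day 0. Treatment shifts both changes, so the formula in step 3 applies with the shifts expressed in SDs of change. Using changes does not by itself remove the artefact.

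**The case against.** The strongest reply is that this is loose Discussion prose and not an analysis error. Elsewhere the article is more modest: the abstract speaks of a possible mechanism, and section 2.9 says that pathways will be explored. In the sentence about a chain of evidence, the word causal can be read as qualifying the omics improvements, which are a randomised effect. Section 2.15 sets no significance threshold for the correlations and no rule by which one would confirm the hypothesis. How the arms are handled, or a mediation model, could be in an analysis plan that is not shown.

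Much of this stands, and it rules out several stronger readings that a reader might reach:
- **That the arms will be pooled.** The text does not say so, and the table applies only if they are.
- **That a positive correlation is assured.** The sign follows the directions of the two shifts, the expected r is at most 0.17 over the range shown, and with small shifts the rate is close to nominal.
- **That the whole hypothesis rests on correlation.** Treatment-to-flora and treatment-to-symptom effects have randomised comparisons.
- **That baseline is ignored.** Section 1 sets improvement against changes in flora, which goes part of the way.

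It does not answer the mismatch on the page. The words by modifying the intestinal flora assert the third link, on any reading of causal, and the method named for that link cannot support it whether or not the arms are pooled.

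**Conclusion.** The point holds as a mismatch between a stated mechanistic hypothesis and the analyses named to support it. Correlation cannot establish that P9 acts through the flora. Within an arm, flora and symptoms remain open to common causes that randomisation does not balance with respect to each other.

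The size of the added risk from pooling is conditional. It runs from about 6% false significance for a 0.2 SD feature shift to 60–70% for 2 SD, per feature and uncorrected, against about 5% with arm adjustment. These figures assume pooled arms, normal variables, no within-arm link, and the plan's 0.5 SD effect on bowel-movement frequency. The document gives no feature shift, and no effect size for the other symptoms.

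The consequence is limited to the mechanistic conclusion. The primary efficacy comparison and the other randomised comparisons are unaffected.

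**What to change.** - **Section 3.** Describe the association of flora and metabolite changes with symptoms as exploratory, and not as evidence that P9 acts through the flora. Keep causal language for the randomised effects of treatment.
- **Section 2.15.** Compute correlations on change from day 0, either within each arm or as partial correlations adjusted for arm. State that Benjamini–Hochberg covers the whole correlation matrix.
- **Optional.** Repeat the analysis without the administered strain's own reads. This is at most a sensitivity analysis.
- **If a mediation claim is wanted.** Arm-adjusted correlation does not prove it either. It needs a prespecified mediation model with its assumption of no unmeasured mediator–outcome confounding stated openly.

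The cost is some rewording, a small change to analysis code and a more modest mechanistic claim. No extra data are needed.

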### 3.1. Trial Status

This study started recruiting patients on October 1, 2020. To date, 130 patients have been enrolled. Enrolment is expected to be completed by May 31, 2022, and all follow-up visits are expected to be completed by July 31, 2022. The protocol is version 2.0, and the date of the edition is 10 September 2020.

## Figures and Tables

**Figure 1 fig1:**
[figure not shown]
Flowchart of the protocol.

**Figure 2 fig2:**
[figure not shown]
Defecation diary.

**Table 1 tab1:** Study and follow-up schedule.

Item		Screening period (preadministration observation period)		Observation period during administration		Postadministration observation period
		Visit 0	Visit 1	Visit 2	Visit 3	Visit 4
		(Days −14 to −1)	Day 0	Day 14	Day 28	Day 42
Collection of volunteers' basic information	√					
Screening	√					
Signing informed consent form	√					
Stool test (including occult blood)	√					
Defecation diary	Completed online daily					
Primary outcomes	Weekly mean frequency of CSBMs		√	√	√	√

Secondary outcomes	Weekly mean frequency of CSBMs ≥3		√	√	√	√
	Weekly mean frequency of SBMs		√	√	√	√
	Weekly mean stool appearance score		√	√	√	√
	Weekly mean difficulty of passing stool score		√	√	√	√
	Weekly mean stool appearance score		√	√	√	√
	Weekly mean difficulty of passing stool score		√	√	√	√
	WPUAMA		√	√	√	√
	Quality-of-life score		√	√	√	√
	Emotional state score		√	√	√	√
	Gut microbiome		√		√	√
	Faecal metabolome		√		√	√

Safety measures	Adverse events (AEs)			√	√	√
	Serious adverse events (SAEs)			√	√	√

Verification of compliance with the intervention					√	
Concomitant medications			√	√	√	√

*Note*. Except for the quality-of-life score and emotional state score, the other outcome measures are calculated from the defecation diary.

**Table 2 tab2:** The comparisons of methodologies among the present and previous RCTs related to the effect of probiotics on chronic constipation.

Study	Design	Allocation concealment/Blinding/ITT analysis/Description of withdrawals or dropouts	Sample size (probiotics:control)	Population	Age (years)	Diagnostic criteria	Intervention	Comparator	Probiotic strain	Outcomes	Daily dosage (CFUs)	Study stage (duration)
Agrawal [68]	Randomized, double-blind, controlled, parallel group study	Yes/Yes/Yes/Yes	17/17	Irritable bowel syndrome with constipation in females	20–69	Rome III criteria for constipation predominant IBS	A fermented milk containing probiotics	A milk-based nonfermented dairy product	*Bifidobacterium lactis*	Abdominal distension, gastrointestinal transit, abdominal symptoms, and bowel habit	1.25 × 10^10^	Screening period/baseline (11 days), administration period (28 days), postadministration period (7 days)
Holma [64]	Randomized, controlled, unblinded, 2 × 2 factorial design	Unclear/Unclear/No/No	10/12/11/10/8^a^	Adults with self-reported constipation	22–78	<5 defecations/week without laxatives or <7 defecations/week with laxatives, and self-reported constipation	Whole-grain rye bread or *Lactobacillus rhamnosus* GG (LGG) or whole-grain rye bread + LGG	Laxatives or white wheat bread	Cultured buttermilk supplemented with *Lactobacillus* GG	Faecal weight, pH, short-chain fatty acids (SCFA) and bacterial enzyme activities, total intestinal transit time (TITT), and breath hydrogen	2 × 10^10^	Baseline period (1 wk)-intervention period (3 wks)
Hongisto [69]	Randomized, controlled, 2 × 2 factorial design	No/No/No/No	14/15/16/14^b^	Women with self-reported constipation	18–57	Feelings of reduced/less-frequent bowel movements, as well as straining at defecation	Fibre-rich rye bread + *Lactobacillus rhamnosus* GG (LGG)	Fibre-rich rye bread, LGG, or low-fibre toast	*Lactobacillus* GG	TITT, faecal frequency and consistency, difficulty in defecation, and gastrointestinal symptoms	1.5 × 10^10^	Screening/baseline period (1 wk)-administration period (3 wks)-postadministration period (3 wks)
Malpeli [70]	Randomized, double-blind, placebo-controlled and crossover	Yes/Yes/No/Yes	28/35	Healthy women	21–60	Those with a slow transit perception and/or abdominal pain (bloating) or slow transit (functional constipation) according to Rome III criteria	The synbiotic yoghurt contained the test probiotics	The standard yoghurt	*Bifidobacterium infantis* and *Lactobacillus casei*	Intestinal transit time, voiding frequency, stool consistency and bloating, intestinal flora	10^9^-10^10^	Screening/baseline period (15 days)-administration period (15 days)-washout period (15 days)-administration period (15 days)
Waller [71]	Sex-stratified, triple-blind, placebo-controlled, parallel-group, dose-ranging study	Unclear/Yes/No/Yes	33/33/34^c^	Adults with constipation	25–65	Self-report of stool type 2–4 on the Bristol Stool Chart and an average of 1–3 bowel movements per week.	The capsules contained the test probiotics	Placebo	*Bifidobacterium lactis*	Food frequency, whole gut transit time, functional gastrointestinal symptom frequency	17.2 × 10^9^ or 1.8 × 10^9^	Screening/baseline period (7 days)-administration period (14 days)
Krammer [72]	Randomized double-blind placebo-controlled trial	Unclear/Yes/No/No	12/12	Female adults with chronic constipation	Unclear (∼50)	Transit time >72 h.	Fermented milk drink containing test probiotics	Placebo	*Lactobacillus casei* Shirota (LcS)	Colonic transit time, stool frequency and consistency, constipation-related and gastrointestinal symptoms	6.5 × 10^9^	Screening/baseline period (2 wks)-administration period (4 wks)- postadministration period (4 wks)
Bazzocchi [73]	Randomized double-blind, controlled trial	Yes/Yes/No/No	17/12	Patients with severe functional constipation	19–65	Constipation consecutively matching the Rome III diagnostic criteria for functional constipation	A synergic mixture of the prebiotic psyllium fibre and five probiotic strains	Maltodextrin	*L. plantarum*, *L. acidophilus* and *L. rhamnosus* and *B. longum spp. longum* and *B. breve* species	% Bowel motions with normal stools, decrease in Agachan–Wexner score for constipation severity, increase in faecal levels of *Lactobacillus* and *Bifidobacterium*	unclear	Screening/baseline period (2 wks)-administration period (8 wks)
Cudmore [74]	Randomized, double-blind, placebo-controlled clinical study	Yes/Yes/Yes/Yes	35/34	Adults with chronic, functional constipation	18–80	Rome III diagnostic criteria for functional constipation	5 g sachet containing test probiotics	Placebo	*L. rhamnosus*, *B. bifidum*, *L. acidophilus*, *L. plantarum*, *Lactobacillus bulgaricus*	Number of bowel movements, stool consistency, quality of life, constipation symptoms, reduced laxative use by the subjects	1.2 × 10^9^	Screening/baseline period (14 d)-administration period (7 d)
Eskesen [65]	Randomized, double-blind, placebo-controlled	Yes/Yes/Yes/No	343/452/453^d^	Healthy subjects with constipation	18–70	Low defecation frequency (2–4 times/week) and complaints of general abdominal discomfort	Probiotic strain in capsule form	Placebo	*Bifidobacterium animalis* subsp. *Lactis*	Defecation frequency and gastrointestinal well-being responder rates, symptom severity scores for abdominal pain and bloating	1 × 10^9^ or 10 × 10^9^	Screening/baseline period (2 wks)-administration period (4 wks)
Mazlyn, [75]	Randomized, double-blind, placebo-controlled	Unclear/Yes/yes/Yes	47/43	Adults with functional constipation	18–60	Rome II criteria	Shirota fermented milk containing the test probiotics	Placebo	*Lactobacillus casei* strain Shirota	Constipation severity, stool frequency, stool consistency and quantity	3.0 × 10^10^	Screening/baseline period (2 wks)-administration period (4 wks)
Ojetti [76]	Randomized, double-blind, placebo-controlled	Unclear/Yes/yes/Yes	20/20	Adults with functional constipation	Unclear (approximately 36 ± 15)	Rome III	Probiotic tablets containing the test probiotics	Placebo	*Lactobacillus reuteri*	Bowel movements/week frequency, stool consistency according to BSS	2 × 10^8^	Administration period (4 wks)
Tanaka [77]	Randomized, double-blind, placebo-controlled	Unclear/Yes/Unclear/Yes	18/20	Adults with constipation	25–59	Frequency of bowel movements of <5.0 times/week assessed using a questionnaire	Milk-like drink containing test probiotics	Placebo	*B. animalis* subsp. *lactis*	Intestinal *Bifidobacteria*, frequency of defecation	1.5 × 10^10^	Screening/baseline period (2 wks)-administration period (8 wks)
Waitzberg [78]	Randomized, double-blind, placebo-controlled	Unclear/Yes/Unclear/Yes	50/50	Constipated adult women	18–75	Rome III	Synbiotic containing multiple probiotics	Placebo	*L. paracasei*, *L. rhamnosus*, *L. acidophilus*, *B. lactis*	Stool frequency, consistency and shape, abdominal pain, bloating and flatulence, constipation intensity	10^8^-10^9^	Screening/baseline period (1 wk)-administration period (30 days)
Yang [79]	Randomized, placebo-controlled	Unclear/Unclear/Yes/No	59/56	Adult females with constipation	25–65	Less than three stools per week, increased stool hardness, nonorganic constipation and habitual constipation	Fermented milk contains probiotics	Acidified milk	*B. lactis*	Stool frequency, defecation condition scores, stool consistency and food intake, safety evaluation	1.25 × 10^10^	Screening/baseline period (1 wk)-administration period (2 wks)
Koebnick [80]	Randomized, double-blind, placebo-controlled	Unclear/Yes/Unclear/No	35/35	Adults with chronic idiopathic constipation	18–70	NA	Probiotic beverage	Placebo	*L. casei* strain Shirota	Severity of constipation, defecation frequency, stool consistency, occurrence and degree of flatulence, occurrence, and degree of bloating	6.5 × 10^9^	Screening/baseline period (2 wks)-administration period (4 wks)
Bu [81]	Randomized, double-blind, placebo-controlled	Yes/Yes/Yes/Yes	18/18/9^e^	Children with chronic constipation	<10	Stool frequency of <3 times per week for >2 months and at least one of the following minor criteria: anal fissures with bleeding due to constipation, faecal soiling, or passage of large and hard stool	Capsules containing probiotics	Magnesium oxide (traditional laxative) or placebo	*L. casei rhamnosus*	Frequency of daily bowel movements, stool consistency, abdominal pain, faecal soiling, intestinal flora	8 × 10^8^	Administration period (4 wks)
Banaszkiewicz [82]	Randomized, double-blind, placebo-controlled	Yes/Yes/Yes/No	43/41	Children with constipation	2–16	<3 spontaneous bowel movements per week for at least 12 weeks	Lactulose with *Lactobacillus* GG	Lactulose with placebo	*L. rhamnosus* GG	Greater than or equal to 3 spontaneous BMs per week with no episodes of faecal soiling, the number of BMs per week, number of episodes of faecal soiling per week, stool consistency, and straining frequency per week, percentage of patients using laxatives was assessed at 24 weeks	2 × 10^9^	Administration period (12 wks)-postadministration period
Bouvier [83]	Double blind, placebo-controlled parallel study	Yes/Yes/No/No	36/36	Healthy adults	21–42	Normally indicated by medical examination and not taking any medication for at least four weeks	Fermented milk containing the test probiotics	Placebo milk	*B. animalis*	Colonic transit time	9.75 × 10^10^	Screening/baseline period (10 days)-administration period (11 days)
Marteau [84]	Double-blind, randomized, controlled study	Unclear/Yes/No/No	17/15	Healthy women	18–45	Judged by a medical examination	Fermented milk containing the probiotics	Fermented milk	*B. animalis* strain	Total and sigmoid transit times, the other transit times, faecal weight, pH, bacterial mass, and bile acids	0.19–1.9 × 10^10^	Screening/baseline period (10 days)-administration period (10 days)-washout period (10 days)-administration period (10 day)
Merenstein [85]	Triple-blind, placebo-controlled, two-period crossover trial	Yes/Yes/Yes/Yes	34/34	Women	18–65	Self-reported history of straining during bowel movements or hard or lumpy stools in the past 2 years	Yoghurt containing the test probiotics	Yoghurt	*B. animalis ssp. lactis*	Colonic transit time, the number of bowel movements/week, QOL, frequency of bowel movements over 2 weeks, frequency of constipated stools, % positive for *B. animalis* ssp*. Lactis*, daily diet, compliance	2.0–5.6 × 10^10^	Screening/baseline period (duration is unclear)-administration period (14 days)-washout period (6 wks)-administration period (14 days)
Ishizuka [86]	Placebo-controlled double-blind, crossover	Unclear/Yes/Yes/Yes/No	12/12	Adults suffering from constipation	20–23	Number of defecations is less than or equal to 5.0 times/week	Milk-like drink containing the test probiotics	Milk-like drink	*B. lactis*	Intestinal *Bifidobacteria*	1 × 10^10^	Screening/baseline period (2 wks)-administration period (2 wks)-washout period (2 wks)-administration period (2 wks)
Del Piano [87]	Randomized, double-blind, placebo-controlled study	Unclear/Yes/Yes/Yes/Yes	80/110/110^f^	Healthy volunteers with evacuation disorders and hard stools	24–71	Judged by a complete physical examination, normal values of laboratory tests, and no evidence of gastrointestinal disease on plain abdominal X-ray and ultrasound	A half glass of water containing the test probiotics	Placebo	Mixture of *L. plantarum* and *B. breve* or *B. animalis* subspecies *lactis*	Ease of expulsion, number of weekly evacuations, anal itching, burning, and pain abdominal bloating, sensation of complete emptying	5 × 10^9^ or 2.5 × 10^9^	Screening/baseline period (7 days)-observation period during administration (30 days)
Riezzo [88]	Randomized, double-blind, placebo-controlled	Unclear/Yes/No/Yes	28/28	Adults with functional constipation	19–65	Rome III criteria for FC without matching Rome criteria for IBS	*L. reuteri* DSM 17938	Placebo	*L. reuteri*	CSS, PAC-QOL	2 × 10^8^ and 4 × 10^8^	Screening/baseline period (7 days)-observation period 1 during administration (15 days with the high dosage)-observation period 2 during administration (90 days with the low dosage)
Riezzo [89]	Randomized, double-blind, crossover study	Unclear/Yes/Yes/Yes	10/10	Adults with functional constipation	19–70	Rome Criteria III for constipation 20, Constipation Scoring System (CSS)	Probiotic-enriched artichokes	Artichokes	*L. paracasei*	Stool consistency, GSRS sum score, SCFAs, colonic transit time	2 × 10^10^	Screening/baseline period (7 days)-observation period during administration (15 days)-washout period (4 wk)-observation period during administration (15 days)
Dimidi [46]	Randomized, double-blind, placebo-controlled	Unclear/Yes/Yes/Yes	37/38	General population with mild constipation	18–65	Modified Rome III diagnostic criteria for functional constipation	Milk powder with probiotics	Placebo milk powder	*B. lactis*	Whole gut transit time, regional gut transit time, constipation severity, stool frequency and stool consistency, QOL, gut microbiota composition, safety outcomes	1.5 × 10^10^	Screening/baseline period (duration is unclear)-observation period during administration (4 wks)-postadministration observation period (8 wks)
Mirghafourvand [90]	Randomized, triple-blind, placebo-controlled	Unclear/Yes/No/Yes	29/28	Constipated pregnant women with a gestational age of 24–28 weeks	>18	Rome III criteria	Probiotic yoghurt containing the test probiotics	Conventional yoghurts	*L. acidophilus* and *B. lactis*	The defecation frequency, stool consistency, straining during defecation, sensation of anorectal obstruction, sensation of incomplete evacuation and manual manoeuvres to facilitate defecation, the amount of defecation, stool colour, and QOL	4.8 × 10^8^	Screening/baseline period (duration is unclear)-observation period during administration (4 wks)-postadministration observation period (2 wks)
Favretto [66]	Randomized controlled trial	Unclear/No/No/No	15/15	Constipated women	20–60	Rome III consensus	Fresh cheese containing the test probiotics	Regular fresh cheese	*B. lactis*	Symptoms of Rome III criteria	1 × 10^8^	Screening/baseline period (duration is unclear)-observation period during administration (30 d)
De Paula [91]	Open, randomized, controlled study in parallel groups with intercrossing	Yes/No/No/Yes	Varied according to different outcomes	Women with functional constipation (266) and women without constipation (112)	18–55	Rome II criteria	Dessert with probiotics	Lacteous dessert	*B. animalis*	Stool frequency >5/week, stool frequency >3/week, stool shape, straining effort and pain during bowel evacuation, stool frequency (bowel movements/week), stool shape, pain and straining effort associated with bowel evacuation	1 × 10^8^	Screening/baseline period (duration is unclear)-observation period during administration (2 wks)-observation period during cross-administration (2 wks)
Ding [92]	Prospective Randomized Trial	Yes/Yes/No/Yes	48/45	Patients with slow transit constipation	<18	Rome III criteria for chronic constipation	Synbiotic containing the test probiotics	Placebo	Unclear	Stool frequency and consistency, colonic transit time (CTT), evacuation and abdominal symptoms, patient assessment of constipation symptoms, gastrointestinal QOL index scores, satisfaction scores, and adverse events	unclear	Screening/baseline period (duration is unclear)-observation period during administration (12 wks)
Fateh [93]	Double-blind, randomized, placebo-controlled trial	Unclear/Yes/No/no	31/29	Young men suffering from functional constipation	>18	Rome III criteria for chronic constipation	Synbiotic mixture of probiotics	Capsules	*L. casei*, *L. rhamnosus*, *Streptococcus thermophilus*, *B. breve*, *L. acidophilus*, *B. longum*, *L. bulgaricus*	Stool frequency per week, overall score of patient assessment of constipation symptoms, the Bristol Stool Form Scale, abdominal symptoms score, rectal symptoms score, stool symptoms score	1 × 10^8^	Screening/baseline period (duration is unclear)-observation period during administration (4 wks)
Jayasimhan [94]	Randomized, double-blind, placebo-controlled	Yes/Yes/Yes/Yes	50/58	Constipated adults	18–81	Rome III criteria for chronic constipation	Microbial cell preparation containing probiotics	Placebo	*L. acidophilus*, *L. casei*, *L. lactis*, *B. bifidum*, *B. longum* and *B. infantis*	Frequency of bowel movements per week, self-perception of the improvement in symptoms (straining, lumpy or hard stool, sensation of incomplete evacuation, sensation of anorectal blockage and manual manoeuvres to aid in defecation)	3 × 10^10^	Screening/baseline period (duration is unclear)-observation period during administration (1 wk)
